## Abstract

**Background::**

Dysmenorrhea seriously affects the ability of women to perform normal social activities and decreases their quality of life. Primary dysmenorrhea can be effectively treated with acupuncture. Based on the wrist-ankle acupuncture (WAA) theory, we designed a portable WAA point compression treatment strap that treats diseases by automatically applying pressure to acupuncture points. The proposed study aims to evaluate the immediate analgesic effect of the acupressure wrist-ankle strap in patients with primary dysmenorrhea.

**Methods::**

The study will be a randomized controlled trial conducted from May 1, 2019 to May 30, 2020 that includes 78 students from Shanghai University of Traditional Chinese Medicine who have primary dysmenorrhea and meet the eligibility criteria. Participants will be randomly divided into 2 groups in a 1:1 allocation ratio. The intervention group will use the acupressure wrist-ankle strap equipped with tip compression component parts on the internal side; the control group will use the nonacupressure wrist-ankle strap with the tip compression parts removed. All participants will be treated for 30 minutes on the 1st day of menstruation. The primary outcome is the pain intensity score measured by the visual analog scale. The secondary outcomes are the onset time of analgesia, the pain threshold at Yinlingquan (SP 9), skin temperature at Guanyuan (CV 4), and expectations and satisfaction of patients as investigated via the expectation and treatment credibility scale.

**Discussion::**

This trial will be the 1st study to evaluate the analgesic effect of the acupressure wrist-ankle strap in patients with primary dysmenorrhea. The quality of this study is ensured by the randomization, nonacupressure control, and blinded design. The results may provide evidence for a potential alternative treatment for primary dysmenorrhea and evidence-based proof of the analgesic effect of WAA.

## Introduction

1

Dysmenorrhea is a condition in which pain is experienced in the lower abdomen and lumbosacral area during menstruation. Patients with severe dysmenorrhea have associated nausea, vomiting, diarrhea, and even syncope.^[1]^ Primary dysmenorrhea is more common in unmarried women, as they typically have no organic lesions in the reproductive organs; primary dysmenorrheic pain is mainly caused by uterine muscle spasm or tonic contraction. Secondary dysmenorrhea mainly prevails in married people, mostly due to pelvic inflammation, uterine fibroids, endometriosis, and other diseases.^[2]^ Because of differences in the definition of dysmenorrhea and/or the methods used to measure dysmenorrheic pain, the prevalence of dysmenorrhea varies widely between countries, but generally ranges from 50% to 90%.^[3]^ Primary dysmenorrhea not only causes the abovementioned symptoms, but can also be associated with diseases such as interstitial cystitis, arrhythmia, and irritable bowel syndrome, which seriously affect normal social activities, quality of life, and increase the mental and psychological burden of patients.^[4]^ Furthermore, dysmenorrheic patients may be unable to attend work and school, which has an impact on social economy and education.^[5,6]^ Previous studies reported that 25% to 51% of dysmenorrheic patients are unable to study, work, and live normally.^[7,8]^ Therefore, it is important to investigate ways to reduce the labor loss caused by primary dysmenorrhea and improve the quality of life of patients.

In western medicine, the symptoms of primary dysmenorrhea are treated or controlled using analgesics, nonsteroidal anti-inflammatory drugs, and oral contraceptives. However, these drugs may trigger gastrointestinal reactions and/or affect the central nervous system and metabolism, leading to poor long-term effects, drug resistance, and adverse effects.^[9]^

Acupuncture therapy plays an important role in the clinical treatment of primary dysmenorrhea^[10]^ due to its safety, rapid onset of analgesic effect, low cost, and low incidence of adverse effects.^[11]^ Wrist-ankle acupuncture (WAA) is more readily accepted by patients than traditional acupuncture and electroacupuncture, as WAA is easy to operate and causes very minimal pain and discomfort during the implementation process.^[12]^ A systematic review of WAA for the treatment of pain showed that WAA alone and WAA as an adjuvant therapy were more effective than Western medicine, sham acupuncture, or body acupuncture, with few adverse effects.^[13]^ A series of studies conducted by our research group also showed that WAA has a good analgesic effect,^[14–21]^ and the analgesic effect of WAA for acute low-back pain is immediate.^[18]^ However, WAA requires the operator to master specific techniques and thus needs to be performed by acupuncturists. Hence, our research team developed the acupressure wrist-ankle strap, which is a new portable WAA point compression treatment device^[22]^ that aims to replace the need for acupuncture needles and enable the patients to operate it themselves to obtain pain relief.

Numerous studies have proved that WAA significantly reduces pain in patients with primary dysmenorrhea.^[23–26]^ Our hypothesis is that the acupressure wrist-ankle strap, which stimulates the WAA stimulation, will also produce an immediate analgesic effect in patients with dysmenorrhea, a condition with acute pain. Thus, we designed the randomized controlled trial (RCT) described in this study protocol to evaluate the immediate analgesic effect of the acupressure wrist-ankle strap in patients with primary dysmenorrhea.

## Methods and design

2

### Objectives

2.1

The proposed study has 3 objectives: to determine whether the acupressure wrist-ankle strap has an immediate analgesic effect in patients with primary dysmenorrhea; to explore the possible antidysmenorrheic mechanism of the acupressure wrist-ankle strap; and to explore the factors potentially affecting the therapeutic effect of the acupressure wrist-ankle strap.

### Trial design

2.2

This study is an RCT designed to compare the immediate analgesic effect of the acupressure wrist-ankle strap vs a nonacupressure wrist-ankle strap in the treatment of primary dysmenorrhea. Participants with primary dysmenorrhea will be randomly divided into 2 groups in a 1:1 ratio.

### Participants

2.3

#### Inclusion criteria

2.3.1

The inclusion criteria are: women aged 18 to 30 years; meeting the criteria for the diagnosis of primary dysmenorrhea based on the Primary Dysmenorrhea Consensus Guidelines^[27]^; basic regularity of the menstrual cycle (28 ± 7 days); no ongoing treatment for dysmenorrhea; provision of written informed consent; and mean pain intensity score evaluated by the visual analog scale (VAS) of >2 for 3 consecutive menstrual cycles.

#### Exclusion criteria

2.3.2

The exclusion criteria are: pregnancy, prepregnancy, or lactation; having experienced miscarriage or stillbirth; cardiovascular, hepatic, renal, hematopoietic, and other serious primary diseases or mental disorders; being suspected of having other diseases based on the medical history; having taken any analgesic medications within 24 hours before the intervention.

#### Recruitment

2.3.3

The recruitment targets are undergraduate and graduate students at Shanghai University of Traditional Chinese Medicine. Recruitment posters will be put up on campus.

#### Patient safety

2.3.4

The acupressure wrist-ankle strap should not be worn for too long. It is recommended to take it off after wearing for about 30 minutes to prevent the local blood flow from obstruction and avoid other risk factors. If the participants are still in severe pain after 30-minute treatment with the acupressure wrist-ankle strap, a variety of follow-up treatments will be provided, including traditional acupuncture, moxibustion, and analgesic medications. Participants with continuous high pain after the above treatment will be referred to a general physician or gynecologist to receive other form of treatment.

### Intervention

2.4

All participants will go through a standardized interview in which the details of the study will be explained. All treatments will be performed by the same registered acupuncturist. During the treatment, the subject will be in a supine position. The acupuncturist is responsible for setting up the treatment device, and putting it in place for the participants. The details of treatment will be fully documented in accordance with the CONSORT Statement and the Standards for Reporting Interventions in Controlled Trials of Acupuncture (STRICTA).^[28]^

#### Brief introduction to the portable WAA point compression treatment device

2.4.1

In accordance with the basic principles of WAA therapy, each side of the body is divided into 6 vertical zones, and 1 acupuncture point is defined at the wrist and ankle in each vertical zone. The name of the acupuncture point is the same as that of the corresponding vertical zone. A circular horizontal line is drawn at the level of the diaphragm to divide the body into upper and lower halves. Acupuncture points at the wrist are used to treat pain in the upper body, while acupuncture points at the ankle are used to treat pain in the lower body. The acupuncture point selected for treatment is that with the same numbered name of the corresponding vertical zone where the pain is located^[12]^ (Fig. 1).

**Figure 1 F1:**
[figure not shown]
Wrist-ankle acupuncture zones and needling points. Each side of the body is divided into 6 vertical zones numbered 1 to 6, and a circular horizontal line is drawn at the level of the diaphragm to divide the body into upper and lower halves. One acupuncture point is defined at the wrist or ankle in each vertical zone. The name of the acupuncture point is the same as that of the corresponding vertical zone. Acupuncture points at the wrist are used to treat pain in the upper body, while acupuncture points at the ankle are used to treat pain in the lower body. The acupuncture point selected for treatment is that with the same numbered name that corresponds to the vertical zone where the pain is located.

The portable WAA point compression treatment device,^[22]^ the acupressure wrist-ankle strap, is an instrument developed based on WAA therapy that is used instead of invasive acupuncture treatment (Fig. 2). The wrist-ankle strap has removable compression parts that exert pressure and stimulate the corresponding WAA points (compression points). The wrist-ankle strap is equipped with installation bases for 6 fixed compression parts, corresponding to the positions of 6 compression points on the wrist and ankle. Before being worn by the patient, 1 to 2 compression parts are installed in accordance with the individual acupuncture needs of the patient. When the acupressure wrist-ankle strap is being worn, the tips of the compression parts are located at the compression points. For treatment, compression points upper 1 to upper 6 on the wrist and lower 1 to lower 6 on the ankle will be selected, corresponding to the zones where the pain is identified, in accordance with the theory of WAA. Compression of different wrist-ankle compression points relieves pain located on the corresponding zones.

**Figure 2 F2:**
[figure not shown]
Acupressure wrist-ankle strap as the finished product. (A) The product packaging. (B) The product.

#### Acupressure wrist-ankle strap group (intervention group)

2.4.2

Abdominal pain in patients with primary dysmenorrhea is located on the lower 1 and lower 2 zones. Thus, the bilateral lower 1 and lower 2 acupuncture points will be stimulated. The lower 1 point is located at the medial border of the calcaneus tendon, while the lower 2 point is located at the posterior border of the humerus, both at the level 3 inches above the tip of the medial malleolus. The acupressure wrist-ankle strap will be used to replace the stimulation achieved with acupuncture needles. Two compression parts will be installed inside the wrist-ankle strap for each patient (Fig. 3). Patients will wear a wrist-ankle strap on both sides for 30 minutes, so that both the lower 1 and lower 2 compression points are simultaneously pressed (Fig. 4).

**Figure 3 F3:**
[figure not shown]
Parts of the acupressure wrist-ankle strap. (A) The removable compression parts. (B) Wrist-ankle strap with the compression parts installed. (C) Wrist-ankle strap with the compression parts removed.

**Figure 4 F4:**
[figure not shown]
Application of the wrist-ankle strap to the lower 1 and lower 2 regions. Photographs show (A) unilateral locations of the lower 1 and lower 2 regions, (B) unilateral compressed wrist-ankle strap, and (C) unilateral noncompressed wrist-ankle strap.

#### Nonacupressure wrist-ankle strap group (control group)

2.4.3

Patients will wear a wrist-ankle strap on both sides for 30 minutes as the intervention group, but the compression parts will not be installed on the inside of the straps (Figs. 3 and 4).

### Outcome measures

2.5

#### Primary outcome measures

2.5.1

The primary outcome measure is the abdominal pain intensity score assessed by VAS. Abdominal pain will be quantified using the VAS score as determined on a 100-mm horizontal line (0, no pain; 100, pain intolerable). On the VAS scale, the score is based on the horizontal distance from the leftmost pain free to the edge marked by the patient. The distance represents pain intensity. The VAS will be assessed at baseline (3 minutes before intervention) and at 5, 10, and 30 minutes (after the removal of the wrist-ankle strap).

#### Secondary outcome measures

2.5.2

##### Onset time of analgesia

2.5.2.1

The analgesic onset time is defined as the time taken for the dysmenorrheic pain to be significantly relieved as reported by the participants.

##### Pain threshold measurement

2.5.2.2

The pain threshold will be measured at the Yinlingquan acupoint (SP 9) using a pressure pain detector (YISIDA, Hongkong, China). Measurements will be made 3 minutes before treatment and at the end of treatment (after the acupressure wrist-ankle strap is removed).

##### Skin temperature at Guanyuan acupoint (CV 4)

2.5.2.3

The skin temperature at Guanyuan (CV 4) will be measured using an infrared thermal imager (FLIR ONE, FLIR System, Wilson, Oregon, USA). Measurements will be made 3 minutes before treatment, at the analgesic onset time, and at the end of treatment (after the acupressure wrist-ankle strap is removed).

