### Statistical analysis

2.10

The SPSS for Windows 21.0 will be used for statistical processing. All analyses will be conducted in accordance with the intent-to-treat principle and the per-protocol principle. Measurement data will be expressed as mean ± standard deviation, while count data will be described as number and percentage. The normal distribution test and homogeneity test of variance will be used for measurement data. The value of missing data will be defined based on the last-observation-carried-forward principle. The baseline characteristics of the 2 groups will be analyzed using the *t* test or nonparametric test. If the baseline characteristics are imbalanced, covariance analysis is used to adjust the baseline characteristics. Repeated measures analysis of variance will be adopted to analyze the outcome (analgesic effect) between groups and observed time. If necessary, a mixed model will be used to evaluate the analgesic effect. A general linear model analysis will be used to assess the correlation between patient expectations and the effect. All statistical tests will be performed on both sides, and the difference will be considered statistically significant when *P* < .05.

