The purpose of this proposed RCT is to evaluate the immediate effect of the acupressure wrist-ankle strap in relieving pain caused by primary dysmenorrhea. The immediate analgesic effect of this acupressure wrist-ankle strap will be determined based on VAS scores, and the onset time of dysmenorrheic pain relief. The possible mechanisms of the acupressure wrist-ankle strap will be investigated by recording and observing the change in the pain threshold at Yinlingquan (SP 9), and the temperature change in the Guanyuan (CV 4) area. The CMSS and TCM syndrome scale will be used to analyze the correlation between the analgesic effect of the acupressure wrist-ankle strap and the TCM syndrome and severity of the disease.

The acupressure wrist-ankle strap is a physical therapy method that is portable, nontoxic, and easy to operate. Furthermore, the acupressure wrist-ankle strap is environmentally friendly due to its low-carbon characteristics and can be recycled.

If the proposed RCT can verify our hypothesis that the acupressure wrist-ankle strap is effective, it can be used as an immediate and effective physical intervention to relieve abdominal pain for patients with primary dysmenorrhea. The proposed RTC may also provide evidence for the analgesic effects of WAA and promote the application of WAA in clinical practice.

There exist some limitations of this proposed study. First, we will observe only the effects of one 30-minute treatment session, mainly focusing on the effect of 3 time points during the intervention period, for the main purpose of this study is to evaluate the immediate analgesic effect. Further work will be required to determine the longer-term effect of this device and whether this will be safe and acceptable for patients to use it frequently over several days. Second, the recruitment of participants is restricted to the students of a university with a great proportion of females, to include enough samples in a specific time period and to ensure good compliance of the participants. This will limit the external validity of the results. We will test the effects of this device with more diverse samples in the future study.

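### The middle skin-temperature reading is triggered by pain relief itself, and onset time has no value for women without relief, so comparisons using either are conditioned on response

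*Protocol article*

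**What the plan says.** Protocol article, section 2.5.2.1: "The analgesic onset time is defined as the time taken for the dysmenorrheic pain to be significantly relieved as reported by the participants". No value, ceiling or censoring time is given for a woman who reports no relief.

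Section 2.5.2.3 ties the second of three skin-temperature readings to that event: "Measurements will be made 3 minutes before treatment, at the analgesic onset time, and at the end of treatment".

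Section 2.3.4 (Patient safety) allows for women whom the session does not help: "If the participants are still in severe pain after 30-minute treatment with the acupressure wrist-ankle strap, a variety of follow-up treatments will be provided".

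Section 2.10 has three rules that bear on this:
- For description, "Measurement data will be expressed as mean ± standard deviation".
- For gaps, "The value of missing data will be defined based on the last-observation-carried-forward principle", with no exception.
- For testing, "Repeated measures analysis of variance will be adopted to analyze the outcome (analgesic effect) between groups and observed time", with a mixed model if necessary. No time-to-event method is named. The t test or nonparametric test is mentioned only for baseline characteristics.

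The Discussion relies on both outcomes. The immediate analgesic effect "will be determined based on VAS scores, and the onset time of dysmenorrheic pain relief", and possible mechanisms are to be studied through the pain threshold at SP 9 "and the temperature change in the Guanyuan (CV 4) area".

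**The concern.** Relief is what the strap is meant to change. A reading that exists only when relief occurs, and at the moment it occurs, is selected by the effect under test. If the arms differ in how many women are relieved or how soon, the women contributing an at-onset temperature are no longer the randomised groups, and their readings fall at different elapsed times. A temperature difference at onset could then reflect different relief rates or timing, and not a thermal effect of the strap.

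Onset time raises the same issue. A woman unrelieved at 30 minutes has not supplied a missing number; her onset is known to lie beyond 30 minutes. Leaving her out discards the information that the treatment did not work for her, and LOCF has no earlier onset time to carry forward.

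**Working it through.** **The plan's own figure.** The documents give no figure for onset time or skin temperature. The only stated calculation is the VAS sample size, used here solely to take 39 per arm. With σ = 1.4, ρ = 0.7, M = 4, D1 = 1, two-sided α = 0.05 and power 0.90, n = 2σ²·[(1 + (M − 1)ρ)/M]·(1.960 + 1.282)²/D1² = 31.92. This rounds to 32, as stated, and 32 × 1.2 = 38.4 gives 39.

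**What the rules give each woman**

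| | Onset time | Baseline temperature | At-onset temperature | End temperature |
|---|---|---|---|---|
| Relief within 30 min | recorded | fixed time | recorded, at her own elapsed time | fixed time |
| No relief within 30 min | none (beyond 30 min) | fixed time | none; baseline if LOCF is applied | fixed time |

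Only the onset time and the at-onset temperature depend on response.

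**Size for onset time (illustration).** The relief rates are assumptions. Let p be the proportion relieved by 30 minutes, with exponential onset at rate λ = −ln(1 − p)/30.
- Mean onset among relievers = 1/λ − 30(1 − p)/p.
- Mean time to relief counting every woman up to 30 minutes = p/λ.

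For p = 0.8, λ = 0.0536: 18.64 − 7.50 = 11.14 min among relievers, and 14.91 min over all women. For p = 0.5, λ = 0.0231: 43.28 − 30 = 13.28 min and 21.64 min. The differences are −2.14 and −6.73 min.

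| Assumed relief | Relievers per arm (of 39) | Difference, relievers only | Difference, all women to 30 min | Power, relievers-only t test | Power, log-rank censored at 30 min |
|---|---|---|---|---|---|
| 80% v 50% | 31 v 20 | −2.1 min | −6.7 min | 14% | 85% |
| 70% v 40% | 27 v 16 | −1.7 min | −6.1 min | 9% | 79% |
| 60% v 30% | 23 v 12 | −1.4 min | −5.6 min | 8% | 77% |

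Power is from 3,000 simulated trials per row. If the strap changes only how many women are relieved and not how fast (onset among relievers uniform from 3 to 30 min in both arms), the relievers-only test rejects about 5% of the time and the log-rank test 75–77%.

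**Size for the at-onset temperature (illustration).** Assume the strap has no effect on temperature.
- Suppose every reliever shows the same 0.5 °C change at onset and LOCF gives the others zero. The arm means at 80% v 50% are 0.5 × 0.8 = 0.40 °C and 0.5 × 0.5 = 0.25 °C, a spurious difference of 0.15 °C. It is 0.15 °C for any 30-point gap in relief.
- Suppose instead a linear drift of 0.5 °C over 30 minutes, common to both arms, with an SD of 0.5 °C for the change and LOCF for women without onset. The two-sided 5% test then rejects in 7–11% of trials with exponential onset, and in 13–17% when onset speed is the same in both arms.
- Without LOCF, the same drift under exponential onset at 80% v 50% gives a relievers-only difference of 0.5 × 2.14/30 = 0.04 °C. That is small, but the groups compared are still selected by response.

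The baseline to end-of-treatment difference is zero in expectation in all these cases.

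**The case against.** The strongest reply is that much of this is silence, not error. The protocol article writes down no test for onset time, and an analysis plan that is not shown could censor it at 30 minutes. A reader might infer from the mean ± SD rule and the t or nonparametric test that onset will be compared by a t test among relievers. The text does not support that, because those tests are assigned to baseline characteristics. The power figures show what such an analysis would cost; they do not describe a stated plan.

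A reader might also infer that the whole skin-temperature outcome is compromised. It is not. The pre-treatment and end-of-treatment readings are at fixed times in all women, and the Discussion does not say that its mechanism argument rests on the at-onset reading. Nor is repeated measures ANOVA expressly assigned to temperature; a three-point analysis is one possible use of it.

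The LOCF effect is conditional too. The protocol does not say whether a reading that was never triggered counts as missing, and a spurious difference also needs a temperature change shared by both arms, for which the documents give no value.

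These limits stand. Two things remain. The timing of the middle reading is a stated data-collection rule, and no later analysis plan can supply a reading never taken or align its elapsed times between arms. The LOCF rule is also stated text, without exception. A mixed model without imputation would avoid the inserted zeros, but it would still compare readings whose presence and timing depend on relief.

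**Conclusion.** The point holds for the at-onset temperature reading, for any analysis that includes it, and for onset time. It does not hold for the baseline to end-of-treatment temperature comparison, and the primary VAS outcome and sample size are untouched.

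That the at-onset comparison is conditioned on response follows from the protocol's own rules and needs no assumed figures. Its size is not known, because the documents give no relief rates, temperature drift or temperature SD. The number of women without onset is also unknown: the safety provision shows that lasting severe pain is foreseen, but severe pain at 30 minutes is not identical to never having reported relief. The matter is worth correcting, but it concerns secondary outcomes only.

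**What to change.** 1. **Onset time.** Analyse it as time to event, censored at 30 minutes for women without relief, with Kaplan-Meier curves and a log-rank test. Report the proportion relieved by 30 minutes in each arm.
2. **Skin temperature.** Base the tested comparison on fixed-time readings in all women: the end-of-treatment value adjusted for baseline. For women not yet treated, add a middle reading at a fixed time, such as with the 10-minute VAS.
3. **At-onset temperature.** Report it descriptively, with the number of women contributing in each arm and their elapsed times.
4. **LOCF.** State that it does not apply to onset time or to the at-onset temperature. The end-of-treatment temperature does not need this exemption.

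The cost is some analysis wording and one reading at a time when the participant is already assessed. The at-onset reading is lost as a tested outcome. Recruitment began on May 1, 2019, so women already treated may lack a fixed middle reading. For them the end-of-treatment comparison is still available.
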